### Discontinuation of the Study Interventions

The study interventions are not causally associated with serious adverse effects or adverse drug reactions (ADRs), as reported in previously published studies. However, if appropriate measures are not followed while administering *Janu Basti*, adverse effects, such as mild irritation or skin rashes, may occur at the application site. Similarly, bloating, increased bowel movements, and abdominal pain may develop if *Matra Basti* is not administered correctly. *Laksha Guggulu* may lead to abdominal discomfort, nausea, belching, and skin rashes if not taken as per the physician’s instructions and recommended dose.

If any participant developed any adverse effects, administration of the study interventions was temporarily discontinued, and the participant was closely monitored. If symptoms recurred after reintroducing the study interventions, the participant was withdrawn and provided with appropriate medical care as needed.

If any participant developed a serious adverse event (AE) or treatment-emergent AE during the study period, the participant was withdrawn from the study and provided with appropriate incidental care at the study site (ie, the AIIMS, a tertiary care medical institution). In addition, all the study participants were covered by clinical trial insurance during their participation for medical expenses related to the management of any study-related AEs. Furthermore, the sponsor and the ethics committee were notified within 2 working days using the AE and ADRs reporting format, along with appropriate justification. Causality assessment of all AEs, serious AEs, and ADRs occurred during the study was also conducted.

### Compliance With Trial Interventions During the Study

All participants in the Ayurveda group were provided with an information leaflet containing instructions for the use (dose, frequency, and time of administration) and storage of the study interventions. The participants were also issued a compliance form during the baseline and subsequent follow-up visits to self-report their consistent or irregular use of the trial interventions and to record any missed doses with remarks for missing, which enabled assessment of adherence to the dosing pattern as per the study protocol. During each follow-up visit, participants were asked to return the used, unused, or partially used containers of the study interventions to the investigators to assess adherence and cross-check with the participant’s self-reported compliance form.

Participants who did not adhere to the study protocol, did not have ≥80% compliance, developed any study-related AEs resulting in withdrawal from the study at their preference, or withdrew their voluntary consent for participation in the study were withdrawn from the study. If participants consented to data collection during the scheduled follow-ups or at the end of the 180-day period, the data were collected and recorded in the case record form (CRF). The data from completed assessments available up to the point of withdrawal will be used for analysis.

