### Statistical Methods

Categorical data will be presented as numbers (percentages) and compared between groups using the chi-square test. Continuous data following normal distributions will be reported as mean (SD), and between-group comparisons will be performed using the independent sample *t* test. Within-group comparisons for normally distributed data will be conducted using the paired sample *t* test or repeated measures ANOVA. Nonnormally distributed data will be reported as median (first and third quartiles), and between-group comparisons will be performed using the Mann-Whitney *U* test. Within-group comparisons will be conducted using the Wilcoxon signed rank test or the Friedman test. A *P* value <.05 will be considered statistically significant. SPSS software (version 29.0; IBM Corp) will be used for statistical analysis.

The modified intention-to-treat analysis approach will be applied to handle missing data. Missing data for all participants with available data from at least 1 visit after baseline (day 30) will be imputed. The last observation carried forward method will be used to impute the missing values.

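### Outcomes collected with consent after withdrawal appear to be left out of the analysis and replaced by carried-forward values

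*Protocol article*

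**What the plan says.** Three statements in the section Compliance With Trial Interventions During the Study follow one another.

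1. Who is withdrawn. The list opens with "Participants who did not adhere to the study protocol, did not have ≥80% compliance" and goes on to study-related adverse events that led the participant to leave, and to withdrawn consent. The section Discontinuation of the Study Interventions adds another trigger: "If any participant developed a serious adverse event (AE) or treatment-emergent AE during the study period, the participant was withdrawn from the study".
2. What happens to later outcomes. They go into the case record form: "If participants consented to data collection during the scheduled follow-ups or at the end of the 180-day period, the data were collected and recorded".
3. What is analysed. "The data from completed assessments available up to the point of withdrawal will be used for analysis".

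Statistical Methods names a modified intention-to-treat approach. It imputes for everyone with at least one visit after baseline and gives the method: "The last observation carried forward method will be used to impute the missing values".

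No section says that the assessments in statement 2 enter the analysis.

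**The concern.** Non-adherence and adverse events are reasons to stop treatment. They arise after randomisation and may depend on the treatment given. Under an intention-to-treat aim, the outcome of such a participant still counts in the randomised group wherever it was measured. Here the plan provides for measuring it and then appears to cut the analysed data at withdrawal, so that LOCF fills the later visits with the last score before withdrawal.

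If symptoms return after treatment stops, the carried-forward score overstates that participant's day-180 improvement. If they continue to ease, it understates it. For those who consented to follow-up, this error could be avoided because the true value was recorded. The uncertainty about which scores form the primary data set could be avoided too.

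**Working it through.** **The plan's own figures.** From Sample Size: difference 20 points, pooled SD 42, two-sided α 0.05, power 80%.

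- n per arm = 2 × [42 × (1.960 + 0.842) / 20]² = 69.2, so 70 when rounded up. An exact t test gives 70.2, so 71. The stated 69 agrees closely: power at 69 per arm is 79.9% by the normal formula.
- Attrition: 69 / 0.90 = 76.7, so 77; or 69 × 1.10 = 75.9, so 76. The stated 75 is within two of either.

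The data-handling question does not alter these numbers.

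**The two readings side by side.** Take a participant withdrawn after day 60 who consents to a day-180 visit.

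| | Day-180 WOMAC used |
|---|---|
| Compliance section as written: data up to withdrawal, then LOCF | Day-60 score |
| Statistical Methods taken alone: impute only what is missing | Observed day-180 score |

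The same participant has two possible primary outcomes. For high-sensitivity C-reactive protein and interleukin-6, measured only at baseline and day 180, the first reading leaves no post-baseline value at all. If baseline were carried forward, the change would be zero by construction.

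**How many.** 0.10 × 75 = 7.5 per arm, or 15 of 150, if all planned attrition were of this kind. Those who declined further collection, or had no post-baseline visit, reduce the number.

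**Effect on the treatment difference.** Let w be the share of an arm whose observed day-180 value is replaced. Let g be the carried-forward improvement minus the observed improvement at day 180. Then

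shift = w(Ayurveda) × g(Ayurveda) − w(control) × g(control).

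Neither w nor g is in the documents. All rows below are assumptions that show the range.

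| w Ayurveda | w control | g Ayurveda | g control | Shift (points) |
|---|---|---|---|---|
| 10% | 10% | 20 | 20 | 2.0 − 2.0 = 0 |
| 10% | 10% | 20 | 0 | 2.0 − 0 = +2.0 |
| 15% | 5% | 20 | 20 | 3.0 − 1.0 = +2.0 |
| 20% | 0% | 20 | – | 4.0 − 0 = +4.0 |
| 15% | 5% | −10 | −10 | −1.5 + 0.5 = −1.0 |

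Row 2 shows that equal withdrawal rates do not protect the comparison if the gap differs between arms.

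**Effect on the error rate.** The standard error of the difference is 42 × √(2/75) = 6.86. With no true difference, the two-sided rejection rate under shift s is 1 − Φ(1.96 − s/6.86) + Φ(−1.96 − s/6.86). For s = 2 this is 6.0%, and for s = 4 it is 9.0%, against the nominal 5.0%.

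**The case against.** The best defence is textual. The sentence on analysed data does not say that nothing else will be used. The withdrawn group includes people who revoked consent, and for them using data up to withdrawal is correct. A collected day-180 score is not missing, so the LOCF rule need not touch it. This stands as a possible reading, and it is why the point cannot be put as a flat statement that the plan discards real outcomes. It does not remove the problem: the article never says that the sentence is confined to people who refused further collection, and two analysts could follow the text to two different results.

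Three stronger claims are tempting, and the documents do not support them.

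- *The problem falls mostly on the Ayurveda arm.* The section does begin with that arm: "All participants in the Ayurveda group were provided with an information leaflet containing instructions for the use". It describes no separate compliance procedure for controls, and the Ayurveda regimen has more components to adhere to. But the compliance form goes to participants without naming an arm ("The participants were also issued a compliance form during the baseline and subsequent follow-up visits"), the withdrawal triggers cover all participants, and the 10% attrition figure is applied to both arms alike. Imbalance is plausible but not established.
- *Non-compliant participants are excluded.* Statistical Methods keeps anyone with a post-baseline visit and sets no compliance condition. The question is which values represent them, not whether they are counted.
- *The error per participant is very large.* Suppose an improvement of 40 points, linear over 180 days, and withdrawal at day 60. LOCF would credit 40 × 60/180 = 13.3 points, an apparent gap of 26.7. That compares LOCF with the course of someone who stayed on treatment. The relevant comparator is the value actually observed after withdrawal, which the documents do not give.

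It is also fair to say that the affected group may be small. The abstract reports that all participants completed the study. That may mean only that follow-up has ended, and no count of withdrawals is given.

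**Conclusion.** The point holds in limited form. The article provides for consented outcome collection after withdrawal, then describes the analysed data as those up to withdrawal, with LOCF thereafter. On the plain reading, observed day-180 outcomes of withdrawn but consenting participants give way to earlier scores, against the stated modified intention-to-treat approach. On the alternative reading they do not. The two sections must be reconciled either way.

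The size cannot be fixed from the documents. The count of 7 to 8 per arm rests on all the planned attrition being withdrawal with consent to further collection, so it is the highest figure consistent with that 10%. The range of −1 to +4 points, and error rates up to 9.0%, rest on assumed replacement shares and gaps, with the 4-point case needing a fifth of one arm and none of the other. No shift at all is also possible. The case for acting is that the ambiguity bears on the primary outcome and costs almost nothing to remove.

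**What to change.** Replace the sentence on analysed data in the compliance section with:

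*All outcome assessments collected at scheduled visits, including those collected with consent after discontinuation of study treatment or withdrawal for noncompliance or AEs, will be analysed as observed in the randomised group; only values not collected are treated as missing and imputed under the Statistical Methods section.*

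Carry the same wording into the analysis plan, and report by arm how many participants were withdrawn and how many of them gave post-withdrawal outcomes. Whether LOCF suits the values that remain missing is a separate question.

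The cost is one sentence and a check that post-withdrawal visits are in the analysis file. No new participants or visits are needed, since the article says the consented data were recorded in the case record form. The analysis is in progress and the Limitations section says that the analysing statistician is blinded to allocation, so the rule can be settled and dated before results by arm are known.

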### Study Intervention

Eligible participants in the Ayurveda group received a comprehensive Ayurveda treatment protocol, which included *Matra Basti* with *Ksheerabala Taila* and *Janu Basti* with *Dhanwantara Taila*, along with oral medications—*Laksha Guggulu* and *Muktashukti Bhasma*—for 180 days. The details of the study interventions are provided in Table 1.

**Table 1 table1:** Details of the study interventions.

Intervention (with reference)	Route of administration	Dosage and frequency	*Anupana* (vehicle of administration)	Duration
*Ksheerabala Taila* (API^a^ part II, vol I [35])	Rectal (*Matra Basti*)	60 mL once daily after food	—^b^	14 d every 2 mo for 180 d
*Dhanwantara Taila* (API part II, vol I [35])	Local application over the affected knee (*Janu Basti*)	QS^c^ once daily	—	14 d every 2 mo for 180 d
*Laksha Guggulu* (API part II, vol II [36])	Oral	1 g twice daily after food	Lukewarm water	180 d
*Muktashukti Bhasma* (Pharmacopeial Standards for Ayurvedic Formulations [37])	Oral	250 mg twice daily after food	Lukewarm water	180 d

^a^API: Ayurvedic Pharmacopoeia of India.

^b^Not applicable.

^c^QS: quantity sufficient.

The methodology of the therapeutic procedures, *Matra Basti* and *Janu Basti*, is provided in Multimedia Appendix 1. The participants in the control group will receive standard care (ie, topical application of diclofenac sodium gel twice daily) for 180 days, as recommended in the standard treatment guidelines for the management of osteoarthritis of the knee, issued by the Ministry of Health and Family Welfare, Government of India.

Ayurveda practitioners on the research team dispensed the Ayurveda interventions at the study sites throughout the trial period. Furthermore, paramedical staff trained in *Panchakarma* administered *Matra Basti* and *Janu Basti* to the study participants in the Ayurveda group. The participants were examined every 30 days during the study period. The trial Ayurveda interventions were procured from the Indian Medicines Pharmaceutical Corporation Limited, Ministry of Ayush, Government of India.

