### Sample Size

On the basis of the results from a previous study [11], in which the difference in WOMAC score between the Ayurveda and conventional group after 12 weeks of treatment was 24 points, this study has been designed to have 80% statistical power to detect a difference of at least a 20-point improvement (change from baseline) in the WOMAC score after treatment between the 2 groups (pooled SD 42; 2-sided *t* test, α=.05). To achieve this, 69 participants per group were required. Accounting for an expected attrition rate of 10%, the final sample size for each group was determined to be 75 participants (150 in total).

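### Outcome data are collected with consent after withdrawal, but the protocol names only data up to withdrawal for analysis; read literally with LOCF, recorded later WOMAC scores would be set aside

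*Protocol article*

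**What the plan says.** Three consecutive statements in the protocol article, under Compliance With Trial Interventions During the Study, bear on this point.

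- **Who is withdrawn.** The list begins "Participants who did not adhere to the study protocol, did not have ≥80% compliance, developed any study-related AEs resulting in withdrawal" and ends with participants who withdrew consent.
- **What is collected afterwards.** "If participants consented to data collection during the scheduled follow-ups or at the end of the 180-day period, the data were collected", and entered in the case record form.
- **What is analysed.** "The data from completed assessments available up to the point of withdrawal will be used for analysis".

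Statistical Methods adds a modified intention-to-treat approach, with imputation for participants who have at least one post-baseline visit. The method is given as: "The last observation carried forward method will be used to impute the missing values".

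Outcome Measures makes the change in WOMAC from baseline the primary outcome, with assessments every 30 days to day 180. The Results part of the abstract says that all participants completed the study and that analysis is ongoing.

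**The concern.** The second statement provides for outcome data after withdrawal, and the third sets the analysis boundary at withdrawal. An analyst who follows the third statement to the letter treats everything after withdrawal as unavailable, and LOCF then supplies the day 180 value. A measured outcome would give way to an older score from the same person.

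The affected participants are not a random subset. Three of the four routes to withdrawal (non-adherence, compliance under 80%, adverse events) reflect experience with the assigned treatment, and withdrawing consent may do so too. The arms also differ in burden. Study Intervention gives the Ayurveda arm repeated 14-day cycles of enema and knee-oil procedures plus two oral medicines for 180 days, while the control arm has "topical application of diclofenac sodium gel twice daily". Equal withdrawal in the two arms cannot be taken for granted. If it is unequal, replacing recorded outcomes by earlier scores can move the between-group difference, and the comparison no longer uses the known day 180 outcome of everyone randomised.

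**Working it through.** **Step 1: the statements side by side.**

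| Question | What the protocol article provides | Section |
|---|---|---|
| Are scores obtained after withdrawal? | Yes, with consent, at scheduled visits or at day 180 | Compliance |
| Which data of withdrawn participants are named for analysis? | Completed assessments up to withdrawal | Compliance |
| What happens to missing values? | LOCF | Statistical Methods |
| Is it said anywhere that scores after withdrawal are analysed? | No | – |

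The collection statement directly follows the list of withdrawn participants, so it most plainly refers to collection after withdrawal. The analysis statement comes next and names a narrower set of data.

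**Step 2: inputs for an illustration.** The plan gives no figure for this point. For scale, Sample Size provides a target difference of 20 points, SD 42, 75 per arm and expected attrition of 10%: "Accounting for an expected attrition rate of 10%, the final sample size for each group was determined to be 75 participants". The following are assumptions:

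- day 180 is the time point of the primary comparison;
- *w* is the share of one arm that was withdrawn and has a later recorded score. The 10% is borrowed from planned attrition, which is a different quantity, and the true share could be much smaller;
- *d* is the gap between the carried-forward score and the recorded day 180 score, taken as 5 to 20 points;
- the other arm is unaffected.

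**Step 3: formula.** If a share *w* of an arm is misstated by *d* on average, that arm's mean change moves by *w* × *d*. With both arms affected, the between-group difference moves by *w*₁*d*₁ − *w*₂*d*₂, so equal shifts cancel.

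**Step 4: results, shift in points.**

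| *w* | *d* = 5 | *d* = 10 | *d* = 20 |
|---|---|---|---|
| 5% | 0.25 | 0.5 | 1.0 |
| 10% | 0.5 | 1.0 | 2.0 |
| 20% | 1.0 | 2.0 | 4.0 |

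At *w* = 10%, which is 0.10 × 75 = 7.5 participants, the shift is 0.5 to 2.0 points. Against the 20-point target this is 0.5/20 = 2.5% to 2.0/20 = 10%. The standard error of the difference at the planning values is 42 × √(2/75) = 6.86 points, so the same shift is 0.5/6.86 = 0.07 to 2.0/6.86 = 0.29 standard errors. The 20% row is twice the planned attrition, placed wholly in one arm, and only shows how the formula scales.

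**The case against.** The strongest reply is that the statements are complementary. The list of withdrawals includes people who withdrew consent. On this reading, those who agree to further collection are followed to day 180, and the last statement only assures that data already obtained from the others are kept. It lacks the word 'only'. LOCF, as written, fills missing values, and a recorded score is not missing. The statistical analysis plan, which is not shown, may also settle the matter.

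Much of this stands. A reader might infer that the protocol orders recorded scores to be replaced, and the documents do not say that. What remains is that the analysis statement is written for withdrawn participants generally, comes straight after the provision for later collection, and is not balanced by any statement that later scores are used. This is a stated rule that permits the wrong analysis, not a detail left to another document.

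A second reply is that there may be nobody to whom it applies, since the abstract reports that all participants completed. If that means no withdrawals, the numerical effect is nil. If it means only that follow-up has ended, the point is live. The article gives no withdrawal counts to decide between the two.

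A third reply is that heavier treatment burden in one arm does not show that withdrawal differed. That is correct. It shows only that balance cannot be assumed.

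**Conclusion.** The point holds as a wording that should be corrected before the analysis is final. Read literally with LOCF, it would set recorded later WOMAC scores, including day 180, aside in favour of earlier ones, in a group whose withdrawal is not random. The milder reading is possible, and the text does not rule it out.

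Size and direction cannot be derived, because the documents give neither the number withdrawn, nor how many of them were assessed later, nor how their scores changed. The 0.5 to 2.0 points is an illustration that rests on the assumed *w* and *d* and on placing all affected participants in one arm. A reader might infer that the rule favours the Ayurveda arm or threatens the trial's power. The documents support neither: the sign of the gap is unknown, equal shifts cancel, and the effect may be zero.

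**What to change.** Replace the last sentence of the compliance section with:

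> All outcome data recorded with consent after withdrawal or treatment discontinuation, up to day 180, will be analysed in the randomised arm; imputation applies only to values not recorded.

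Report by arm the number withdrawn and how many of them had later outcome data. This also shows whether the point had any numerical effect.

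The cost is one sentence and a small table. The values are already in the case record form, no new data collection is needed, and the article says analysis is still in progress. The limit of the change is that participants who refused further collection stay missing and still need imputation.

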**Results:**

Recruitment of study participants commenced on October 11, 2022. Currently, all the participants completed the study and the analysis of the study outcomes is ongoing.

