### Limitations

This protocol also has a few limitations, including the open-label design of the study. However, to minimize potential bias in assessing the outcomes, the research staff assigned to assess the study outcomes were blinded to the allocation of participants to the study groups. Furthermore, to mitigate the risk of selective reporting of trial results, the statistician who will analyze the study data will also be blinded to the allocation of participants to the study groups.

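### As written, analysis stops at withdrawal, so recorded later WOMAC scores of participants withdrawn for poor compliance would give way to carried-forward values

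*Protocol article*

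**What the plan says.** The section Compliance With Trial Interventions During the Study makes three statements in sequence.

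- Among those withdrawn from the study are participants who "did not have ≥80% compliance".
- Recording may continue after that: "If participants consented to data collection during the scheduled follow-ups or at the end of the 180-day period, the data were collected" and entered in the case record form.
- The rule for use comes next: "The data from completed assessments available up to the point of withdrawal will be used for analysis".

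The Statistical Methods section names a modified intention-to-treat approach. On who is imputed it says "Missing data for all participants with available data from at least 1 visit after baseline (day 30) will be imputed", and on how, "The last observation carried forward method will be used to impute the missing values". Nothing in the article says whether a score recorded after withdrawal counts as observed.

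The primary outcome is change in WOMAC from baseline, assessed every 30 days to day 180 (Outcome Measures).

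**The concern.** Read together, the two sections let adherence after randomisation decide which primary-outcome values are used. A participant withdrawn for low compliance stays in the analysis set once there is a day-30 visit. If the day-180 WOMAC was then collected with consent, the cut-off sets it aside and LOCF supplies an older score. That discards the observation that best answers the trial's question, which is about management over 180 days. It also sits badly with an intention-to-treat principle.

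The arms could be affected unequally. The Ayurveda arm has daily rectal and knee oil procedures for 14 days in every 2 months, plus two oral products twice daily. The control arm applies a gel twice daily (Study Intervention). Different rates of compliance withdrawal are therefore plausible, though none are reported. If the rates differ, the WOMAC difference between groups moves. The direction cannot be predicted: an early gain carried forward flatters an arm, while a score carried from before benefit has built up understates it.

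**Working it through.** **What the rule does to one participant.** Suppose someone is withdrawn for compliance at day 60 and consents to further collection.

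| Visit | Recorded? | Used under a cut-off | Used if all recorded data count |
|---|---|---|---|
| Days 30, 60 | yes | observed | observed |
| Days 90 to 150 | if attended | day-60 score carried | observed where attended |
| Day 180 | yes | day-60 score carried | observed |

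The two readings give different day-180 values for the same person.

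**Inputs from the Sample Size section.** Target difference 20 points, pooled SD 42, two-sided α 0.05, power 80%, 69 per group, 10% attrition, 75 per group after inflation.

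**The plan's own figure.** n per group = 2 × (1.960 + 0.842)² × 42² / 20² = 69.2, so 70 against the stated 69. Power at 69 is 79.9% by the normal approximation. Attrition: 69 / 0.90 = 76.7, so 77 against the stated 75. Both are close, and nothing here turns on the gap.

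**Shift in the group difference.** Let k be the net number affected in one arm (the excess over the other arm, taking the same gap in both). Let d be the carried minus the observed day-180 WOMAC. Both are assumed, because the article gives neither.

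Shift = (k / 75) × d

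For scale, SE of the difference = 42 × √(2/75) = 6.86.

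| k of 75 | d = 10 | d = 20 | d = 30 | At d = 20, share of 20-point target | At d = 20, in SE |
|---|---|---|---|---|---|
| 0 | 0 | 0 | 0 | 0% | 0 |
| 1 | 0.13 | 0.27 | 0.40 | 1.3% | 0.04 |
| 2 | 0.27 | 0.53 | 0.80 | 2.7% | 0.08 |
| 4 | 0.53 | 1.07 | 1.60 | 5.3% | 0.16 |
| 8 | 1.07 | 2.13 | 3.20 | 10.7% | 0.31 |

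The last row is an upper bound under the planned attrition. Since 10% of 75 is 7.5, it treats about all of one arm's expected attrition as compliance withdrawals with later data and no offset in the other arm.

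**Effect on the test (75 per arm, SD 42, normal approximation).** Power for a true 20-point difference is 83.0% with no shift. A 0.5-point shift against the effect (5% of one arm, d = 10) gives 81.1%. A 2.0-point shift (10% of one arm, d = 20) gives 74.7%. With no true difference, the same shifts take the two-sided rejection rate from 5% to 5.06% and 5.98%.

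**The case against.** **The sentence may only be a retention rule.** It does not say that only pre-withdrawal data are used. The withdrawal list also covers people who revoke consent, and for them a promise to keep data already gathered is ordinary. It would be odd to seek consent for day-180 data, record them and then ignore them. This reading is possible and cannot be excluded. But the sentence directly follows the one on continued collection, sets withdrawal as the end point, and is the only statement of which data from withdrawn participants are analysed. A cut-off is the more natural reading.

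**A recorded score is not missing, so LOCF should not touch it.** This has some force. The Statistical Methods section imputes only missing values, but it does not say that scores recorded after withdrawal count as observed, and the compliance section limits what will be used. The point does not rest on detail left to an unseen analysis plan, because the article itself states a rule.

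**The approach is modified intention-to-treat, and nobody is removed for non-adherence.** This is correct for anyone with a day-30 visit, and it narrows the complaint. What depends on adherence is which of a participant's values are used, not whether the participant is in the set.

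**There may be nobody affected.** The Abstract reports: "Currently, all the participants completed the study and the analysis of the study outcomes is ongoing". If that means no compliance withdrawals, the shift is zero. It could also mean only that follow-up has ended, and no withdrawal count is given.

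**The effect is small.** This is accepted. A 20-point gap equals the whole target difference, and even so 2 of 75 moves the estimate by only 0.08 SE.

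**Conclusion.** The concern holds. On its natural reading, the compliance section sets aside primary-outcome values that were recorded after withdrawal, and the Statistical Methods section puts carried-forward scores in their place. The milder reading remains open, and under it a clarification changes nothing in the analysis.

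The likely effect is small: about 0.3 to 0.8 points for a net 2 of 75 affected, and about 1.1 to 3.2 points at the 8-of-75 bound, for gaps of 10 to 30 points. These figures rest on assumed counts and gaps, and the documents fix neither size nor direction. The change is still worth making because it is cheap, and because choosing between the two readings after the groups have been compared would be a post hoc decision.

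**What to change.** Replace the sentence that ends the compliance section with a rule of this kind: the primary modified intention-to-treat analysis uses every WOMAC assessment recorded, including those collected with consent after withdrawal for non-compliance, and imputes only values that are truly missing.

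Two additions would help but are not essential. Use the 80% compliance threshold only to define a supplementary per-protocol set. Report, by arm and visit, how many participants were withdrawn for compliance and how many of them have later WOMAC data.

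**Timing.** Analysis is described as ongoing, and the Limitations section says "the statistician who will analyze the study data will also be blinded to the allocation of participants to the study groups". The rule can therefore still be fixed blind, provided the groups have not yet been compared; the article does not state that directly.

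**Cost.** One sentence, and use of data already in the case record form. No new visits are needed. The estimate will include less adherent participants and may be smaller, and those without consented later data will still need imputation.
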